### Monitoring

#### Data monitoring

The data will be monitored by MR. Additionally, regular team meetings (every 2 weeks) and supervision sessions (every 1–2 weeks) will be conducted. Adverse events, including data findings as well as occurrences in the consultations, will be reported to the supervising psychological psychotherapist (CH) and the primary sponsor and principal investigator of the study (CK). Interim analyses will only apply to the outcomes that the consultants need for the intervention sessions. No stopping rules have been defined for this trial.

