## Methods/design

### Trial design

This study is a nonblinded two-armed parallel randomised controlled trial (see Additional File 1 for the SPIRIT checklist). The superiority of the VA-V over the German S3-Guideline-based intervention will be evaluated. Participants will be randomly assigned to either the VA-V group or the German S3-Guideline-compliant aftercare group. Random allocation will be performed on a 1:1 ratio basis and covariate-adaptively for gender and type of tumour disease. The assessments will be conducted at baseline (T1), during the intervention (T2, T3), postintervention (T4), and at the 6-month follow-up (T5; see Fig. 1). The VA-V group will receive 12 online intervention sessions. The control group will be an active control group receiving 3 supportive online talks according to the German S3-Guideline [5].

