#### Interventions

*VA-V intervention.* Participants in the VA-V will receive twelve manual-based 50-minute sessions of video-based value-oriented behavioural activation, usually once a week, offered by a trained consultant. The trained consultants will be randomly assigned to the participants. However, due to holidays, illness, or other appointments, there may be 2–3 weeks between two appointments. Both the VA-V and the German S3-Guideline-based intervention will be offered by the same consultants to minimise person effects. If an appointment has been missed, efforts will be made to contact the participant to schedule a new appointment. If a participant wishes to discontinue the intervention, participants will be asked for their reasons. Discontinuations and all deviations of the intervention protocol will be documented.

To ensure treatment integrity and adherence to the intervention protocol, the intervention will be carried out by specially trained scientific staff (psychologists and pedagogues) of the Department of Clinical Psychology and Psychotherapy based on the VA-V manual and supervised by a psychological psychotherapist. Training and supervision will be provided by the author of the VA-V manual (CH), a psychological psychotherapist. In addition, it is planned that the conducting scientific staff will participate in a specific curriculum for psycho-oncological qualification―the advanced training in psychosocial oncology (Weiterbildung Psychosoziale Onkologie) certified by the German Cancer Society―during the project period. In the VA-V condition, all sessions will be video-graphed. The videographies will be used for quality assurance in terms of treatment integrity and supervision and―if the participants separately consented―for anonymised analysis of specific session parts (e.g. a thought experiment).

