
*German S3-Guideline-based intervention.* Participants in the active control group will receive aftercare according to the German S3-Guideline ‘Psycho-oncological diagnosis, counselling and treatment of adult cancer patients’ [5]. They will receive three supportive talks at roughly the same times as the intervention group will receive sessions 1, 6, and 12. Supportive talks will cover fatigue management and relaxation techniques.

The German S3-Guideline-based intervention will thus involve more comprehensive aftercare than care as usual (CAU), as large gaps in care exist in outpatient cancer counselling and in the provision of outpatient psycho-oncological and psychosocial services [19]. Many of the spatial planning regions in Germany are underserved or have a low coverage rate (54 % have a coverage rate < 50 %, 30 % have a coverage rate between 50 % and < 75 %) regarding outpatient psycho-oncological care [6].

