#### Outcomes

Various empirically validated questionnaires will be used to collect the data. The participants will complete these questionnaires online on a survey portal (ViVA platform) specially designed for the study. The programming of the ViVA platform is based on LimeSurvey (https://www.limesurvey.org). The questionnaires themselves will be created in LimeSurvey, while the ViVA platform will enable a customised user interface for participants and research staff. For an overview of the study outcome measures, see Tables 1 and 2. Participants will be contacted via the channel they have chosen in advance (e-mail, SMS, or both).

**Table 1 Tab1:** Measurement points and intervention sessions

Measurement/intervention	Content
Baseline measurement (T1)	Po-Bado-KF, NCCN Distress Thermometer, HADS, FBK-R23, SF-12, EQ-5D-5L, ERA^b^, WAI-r^b^, GoalAdjust, FCR7, RRQ
Intervention session 1^a^	Introduction and anamnesis
Intervention session 2	Feedback on diagnostic assessments and psychoeducation
Intervention session 3	Value-goal clarification, introduction to values and the value questionnaire
Intervention session 4	Elaboration of old and new values, goal 1
Intermediate measurement 1 (T2)	GoalAdjust, RRQ, ZUF-8 (only VA-V), WAI-SR (only VA-V)
Intervention session 5	Elaboration of old and new values, goal 2
Intervention session 6^a^	Elaboration of old and new values, goal 3
Intervention session 7	Value-oriented activation, further activity building and dealing with problems
Intervention session 8	Completing the individual activity plan
Intermediate measurement 2 (T3)	GoalAdjust, RRQ, ZUF-8 (only VA-V), WAI-SR (only VA-V)
Intervention session 9	Dealing with specific problems, Problem-solving training 1
Intervention session 10	Problem-solving training 2
Intervention session 11	Problem-solving training 3
Intervention session 12^a^	Closing session, summary, relapse prevention
Post measurement (T4)	HADS, FBK-R23, SF-12, EQ-5D-5L ERA^b^, GoalAdjust, FCR7, ZUF-8 (only VA-V), WAI-SR (only VA-V), RRQ, Closing questionnaire
Catamnesis (6 months post intervention, T5)	HADS, FBK-R23, SF-12, EQ-5D-5L, ERA^b^, GoalAdjust, FCR7, WAI-r^b^, RRQ

^a^ At roughly similar time points the 3 supportive talks in the German S3-Guideline group are scheduled. Content and duration deviate from the intervention group

^b^ Only participants who are not retired due to ill health or old-age

**Table 2 Tab2:** Outcome measures

Measures	T1	T2	T3	T4	T5
Po-Bado-KF	x				

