#### Harms

The study will not give rise to any additional health risks, impairments, or burdens that go beyond what would be expected in everyday life or in the context of another survey or psycho-oncological counselling. It is not assumed that participation in the study will have negative effects on participants, such as anxiety, exhaustion, or discomfort, which go beyond what is experienced in other psycho-oncological consultations. Nevertheless, all adverse events will be documented. Should negative effects occur, these will be closely monitored by a psychological psychotherapist. If a study participant’s symptoms worsen and require more intensive psychotherapeutic treatment, psychological psychotherapists will be available at the university outpatient clinic.

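### One of the two named adverse-event sources is consultations, 12 in VA-V against 3 in control, so adverse-event counts by arm would not be comparable without an identical enquiry in both arms

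*Protocol article*

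**What the plan says.** Under Monitoring, the Data monitoring section says: "Adverse events, including data findings as well as occurrences in the consultations, will be reported to the supervising psychological psychotherapist". The report also goes to the principal investigator. The Harms section adds: "Nevertheless, all adverse events will be documented".

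The contact schedules differ by arm. Trial design states "The VA-V group will receive 12 online intervention sessions" and, for control, "The control group will be an active control group receiving 3 supportive online talks". The Interventions section gives the length and rhythm in VA-V: "Participants in the VA-V will receive twelve manual-based 50-minute sessions of video-based value-oriented behavioural activation, usually once a week". It places the control contacts as follows: "They will receive three supportive talks at roughly the same times as the intervention group will receive sessions 1, 6, and 12". A footnote to Table 1 says of the control talks: "Content and duration deviate from the intervention group". Session recording is described for one arm only: "In the VA-V condition, all sessions will be video-graphed".

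Tables 1 and 2 fix the questionnaires. HADS and FBK-R23 are taken at T1, T4 and T5 in both arms. At T2 and T3 both arms complete GoalAdjust and RRQ; ZUF-8 and WAI-SR are added in VA-V only. A closing questionnaire is listed at T4 without an arm restriction, and its content is not described.

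**The concern.** An event that comes to light because a participant mentions it to a consultant has four times as many scheduled occasions to do so in VA-V as in control. Unless the other source makes up the difference, recorded events depend on how often people are seen as well as on how often events occur.

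Every participant has a diagnosed mental disorder and a Distress Thermometer score of at least 5, so worsening during the trial is realistic. Two things are at stake. First, if adverse events are later tabulated by arm, an excess in VA-V could be a contact artefact. Equally, a real excess could be dismissed as one. Second, worsening that starts between two control talks may come to notice late. The Discussion foresees publication and wide dissemination of the manual if results are positive, so a readable harms record has value.

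**Working it through.** The documents give no adverse-event rate or detection rate, so there is no stated figure to reproduce. The check sets the schedules side by side and then shows how far counts could diverge under stated assumptions.

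**Schedules**

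- Scheduled contacts: 12 in VA-V, 3 in control (Trial design, Interventions). Ratio 12/3 = 4.
- Control talks fall near sessions 1, 6 and 12, so the gaps are 6 − 1 = 5 and 12 − 6 = 6 session intervals. With sessions usually weekly, that is about five and six weeks, and longer when appointments slip.
- T2 follows session 4 and T3 follows session 8. Both fall inside those gaps, but neither carries HADS or FBK-R23. RRQ, a rumination scale, is the nearest common measure.
- The same consultants serve both arms (Interventions). This helps to equalise what is noted per contact, but not the number of contacts.

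**Illustration**

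Assume that each contact detects a given event independently with probability q, that the event can be detected at every contact, and that questionnaire data detect it with probability c, equal in both arms. With k contacts:

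capture = 1 − (1 − c)(1 − q)^k, with k = 12 for VA-V and k = 3 for control.

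With c = 0 and q = 0.10, capture is 1 − 0.9^12 = 0.718 in VA-V and 1 − 0.9^3 = 0.271 in control, a ratio of 2.65. With c = 0.50 and the same q, capture is 1 − 0.5 × 0.9^12 = 0.859 and 1 − 0.5 × 0.9^3 = 0.635, a ratio of 1.35.

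Apparent VA-V to control ratio when the true rates are equal:

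| q per contact | c = 0 | c = 0.25 | c = 0.50 | c = 0.75 |
|---|---|---|---|---|
| 0.02 | 3.66 | 1.40 | 1.15 | 1.05 |
| 0.05 | 3.22 | 1.67 | 1.28 | 1.10 |
| 0.10 | 2.65 | 1.74 | 1.35 | 1.14 |
| 0.20 | 1.91 | 1.54 | 1.30 | 1.13 |
| 0.30 | 1.50 | 1.33 | 1.20 | 1.09 |

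In counts, take the planned 73 per arm and an assumed true risk of 20% in each arm, which gives 73 × 0.20 = 14.6 true events per arm. At q = 0.10 the expected recorded numbers are:

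- c = 0: 10.5 in VA-V against 4.0 in control
- c = 0.50: 12.5 against 9.3
- c = 0.75: 13.6 against 11.9

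Whenever c is equal in both arms, the ratio exceeds 1. Its size turns almost wholly on c, which the documents do not allow one to estimate.

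**The case against.** The strongest reply is that this is an article, with two short sections on monitoring and harms. Adverse-event definitions, prompts and forms commonly sit in a fuller document, and their absence here is no fault. That stands. The point therefore rests only on what the article does fix: consultations as a named source, the 12 and 3 schedule, and the content of T2 and T3.

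Four stronger readings are tempting, and the documents do not support them.

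- A reader might infer that adverse events are found mainly through consultations. The sentence ranks neither source, names data findings first, and is worded as an open list.
- A reader might infer that a planned harms comparison is biased. The Statistical methods section describes none. The concern applies to any counts by arm that are later reported.
- A reader might infer that deterioration in control goes unseen. HADS and FBK-R23 are collected in both arms at T4 and T5, RRQ also at T2 and T3, and those who stop the intervention are still asked to complete questionnaires. What can be missed is worsening that arises and resolves before T4; otherwise it may simply be noticed late. The absence of consultations between T4 and T5 is common to both arms and creates no imbalance.
- A reader might take the c = 0 column as the expected size. It is a worst case in which questionnaires detect nothing. The model also gives each contact the same chance of detection, whereas a control talk covers a longer interval and might draw out more.

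It also cannot be said that no questionnaire asks about unwanted effects, because the T4 closing questionnaire is undescribed and could do so. Even then it would cover T4, not T2, T3 or T5.

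**Conclusion.** The point holds in a limited form. As described, one named route for adverse events is four times as dense in VA-V. The other route has no instrument identified as an adverse-event query, and it carries no HADS or FBK-R23 during treatment. Counts by arm would tend to be higher in VA-V for equal true rates, and worsening between control talks may be noticed only at T4.

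The direction is clear if questionnaire capture and per-contact detection are equal in the two arms. The size is unknown: about 1.5 to 3.7 if consultations are the only source, 1.15 to 1.35 if questionnaires capture half of events, and 1.05 to 1.14 if they capture three quarters. All of these are for assumed q of 0.02 to 0.30. The values of q and c and the 20% risk are assumptions, not figures from the protocol.

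The primary and secondary analyses are untouched, and symptom worsening as such can be compared fairly on HADS and FBK-R23 at T4 and T5. This is an inexpensive improvement to the harms record, not a threat to the trial's main conclusion.

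**What to change.** Add the same short block of self-report adverse-event items to the existing ViVA questionnaires at T2, T3, T4 and T5 in both arms. It could ask about new or worsened psychological symptoms, hospital or crisis contact, and unwanted effects that the participant attributes to the sessions. If the closing questionnaire already holds such items, use the same wording at the other time points.

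Base any summary of adverse events by arm on this block. Report events noted in consultations separately, with the number of contacts held per arm, so that readers can see the difference in exposure to detection.

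The cost is slightly longer questionnaires at four existing measurement points, a protocol and ethics amendment, and some staff time to read the answers. No new visits are needed. Because recruitment had started when the article was written, participants who have already passed some time points would lack the items there, and the report should say so.

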#### Harms

The study will not give rise to any additional health risks, impairments, or burdens that go beyond what would be expected in everyday life or in the context of another survey or psycho-oncological counselling. It is not assumed that participation in the study will have negative effects on participants, such as anxiety, exhaustion, or discomfort, which go beyond what is experienced in other psycho-oncological consultations. Nevertheless, all adverse events will be documented. Should negative effects occur, these will be closely monitored by a psychological psychotherapist. If a study participant’s symptoms worsen and require more intensive psychotherapeutic treatment, psychological psychotherapists will be available at the university outpatient clinic.

## Discussion

This study will evaluate whether the VA-V is effective at reducing distress compared to the German S3-Guideline-compliant aftercare. The consequences of a tumour disease can lead to a relevant and possibly chronic impairment of abilities and of occupational and social participation. A successful adaptation of personal values and goals to a changed life situation can mitigate these effects, as it enables those affected to optimise their everyday life based on their existing abilities and to maintain or restore their ability to work.

One strength of this study is its robust design and follow-up assessment at 6 months allowing evaluation of the long-term effects of VA-V. However, there will also be several challenges in this study. In particular, enrolling a sufficiently large sample may pose a difficulty, which we hope to overcome by recruiting individuals in person at the Rehazentrum Oberharz. To ensure treatment integrity, extensive training prior to implementation, regular supervision, and documentation of the implementation will be essential strategies. These measures will be supported by videographies. If the intervention is discontinued, an attempt will be made to still include the participant in the data collection. Selective dropout in the control group may pose a problem. Nevertheless, three supportive talks constitute more comprehensive aftercare than CAU and may, therefore, motivate participants to complete their study participation.

In summary, this will be the first study to test a manualised VA-V in the aftercare of persons with tumour disease in a randomised controlled trial. If the VA-V proves to be effective, the results will be relevant for improving the aftercare of persons with tumour disease and, as such, be of high public health relevance. The manual of the intervention will be published after a positive evaluation of its effectiveness. Assuming the effectiveness of psycho-oncological treatment, dissemination will be guaranteed by the following points: The manualised intervention will be disseminated through further training offers, including DKG-certified curricula. Various professional groups interested in psycho-oncology, with and without a licence to practise, will be addressed. The knowledge gained regarding the effectiveness and acceptance of video-based treatment will hold great potential for improving psychotherapeutic care in rural areas and for special patient groups with limited mobility.

## Trial status

This is protocol version 1.0 of 7 November 2023. The first participant consented to study participation on 30 October 2023. Recruitment will be completed by 31 December 2024 (or earlier if targeted participant numbers are reached). Important protocol modifications will be communicated to the Ethics Committee and the German Clinical Trials Register, and a protocol amendment will be submitted to TRIALS. The results of the trial will be published in an open access journal once the data analyses will be complete (ca. end of 2025). Participants who wish to receive the results, will be informed of the trial results in an information letter sent via e-mail.

## Data Availability

Data are available upon request due to ethical restrictions. Interested researchers may submit requests to the corresponding author for access to the data. All requests will be assessed by the Data Protection Officer of the University.
